## Abstract

**Background:**

Opioid substitution therapy (also known as ‘opioid agonist therapy’ or ‘medication treatment of opioid use disorder’) is associated with improved health and social outcomes for people who use heroin and other illicit opioids. It is typically managed in the community and is not always continued when people are admitted to hospital. This causes opioid withdrawal, patient-directed discharge, and increased costs. We are establishing a project called iHOST (improving hospital opioid substitution therapy) to address these problems. This is an applied health research project in which we will develop and evaluate an intervention that aims to improve opioid substitution therapy in three acute hospitals in England. The intervention was developed in collaboration with stakeholders including people who use opioids, hospital staff, and other professionals who work with this group. It includes five components: (1) a card that patients can use to help hospital clinicians confirm their opioid substitution therapy, (2) a helpline for patients and staff, (3) an online training module for staff, (4) a clinical guideline for managing opioid withdrawal in hospital, and (5) ‘champion’ roles at each hospital.

**Methods:**

We will do a mixed-methods study including a quasi-experimental quantitative study and a qualitative process evaluation. The primary outcomes for the quantitative study are patient-directed discharge and emergency readmission within 28 days. We will do a difference-in-difference analysis comparing changes in these outcomes for patients at iHOST sites with changes for patients at control hospitals. The process evaluation will use in-depth interviews, focus groups, and site observations with people who use opioids and staff. We will assess acceptability of the intervention, barriers and facilitators to implementation, and contextual factors impacting outcomes.

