**Impact:**

We anticipate that iHOST will improve care for hospital patients who use illicit opioids and/or are receiving community-based opioid substitution therapy. Depending on the results, we will promote the intervention at hospitals across the UK. Dissemination, including through publication, will inform hospital-based services for people who use drugs both in the UK and other countries.

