**Figure 2. f2:**
[figure not shown]
Illustrative difference-in-difference analysis.

**
*Population.*
** The study will use the Hospital Episode Statistics database, which includes all inpatient, outpatient, and A&E episodes at NHS hospitals in England
^
30
^.

The target population is hospital admissions for patients who may benefit from OST. Hospital Episode Statistics does not include records of OST (either in the community or in hospitals), and therefore the study will use a proxy of patients with records of opioid dependence. This will be defined as emergency hospital admissions (i.e., where the field ADMIMETH is 21-25, 2A, 2B, 2C, 2D, or 28) at acute hospitals in England, where the patient was (a) aged 18–64 years at admission; (b) the date of admission was between 12 months before and 12 months after the iHOST site’s implementation dates; and (c) the ICD-10 code F11 (‘mental and behavioural disorders due to use of opioids’) was recorded either at that admission or at another hospital episode for that patient in the preceding 12 months.

We will include patients from the three iHOST sites and from the 50 largest acute hospitals in England where iHOST is not being implemented (when size is defined by the number of patients meeting the criteria listed above). The reason for limiting the control group to the 50 largest hospitals is to exclude small hospitals that may have volatile trends in patient characteristics or outcomes.

**
*Analysis.*
** iHOST will be implemented at different times at each of the three participating hospitals. This means that background trends in outcomes could be different, and the analysis will therefore be done separately for each hospital.

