For analysis of patient-directed discharge, study entry will be at hospital admission. For analysis of readmission, study entry will be at discharge, such that patients who died during the index admission are excluded. We will use a mixed (hierarchical) linear model in which the dependent variable is a binary indicator of the outcome, and independent variables are an interaction term between two binary outcomes: time (i.e., before/after iHOST implementation) and iHOST site or control; a random intercept for the hospital site; and patient-level confounders/covariates. This approach to modelling is known as a ‘linear probability model’, and we have selected it to allow estimation of absolute difference in the risk of outcomes. Confounders will be age, sex, season, primary cause of admission, number of comorbidities, proportion of patients at the hospital who have COVID-19. We will fit the model using a restricted maximum likelihood method implemented in the
R package
lme4
^
31
^. The effect of iHOST will be interpreted from the interaction between time and the control/intervention indicator. Definitions of study variables are included in Extended Data
^
32
^.

**
*Baseline data analysis.*
** We extracted data from Hospital Episode Statistics for the calendar year 2021 to estimate the number of eligible patients and understand their characteristics. The results are summarised in
Table 1. Hospitals are anonymised.

**Table 1. T1:** Number and characteristics of patients with recent diagnoses of opioid dependence in the calendar year 2021, based on preliminary analysis of Hospital Episode Statistics.

Site	Number of patients	Patient-directed discharge N (%)	28-day readmission N (%)	Age (IQR)	Male N (%)	5+ comorbidities N (%)	% patients at hospital with COVID-19
iHOST sites							
A	349	70 (20.1)	101 (28.9)	46 (36-54)	244 (69.9)	143 (41.0)	10.1
B	662	149 (22.5)	214 (32.3)	43 (38-47)	489 (73.9)	195 (29.5)	6.9
C	624	116 (18.6)	148 (23.7)	43 (37-50)	392 (62.8)	182 (29.2)	4.8
Control hospitals							
All	24604	4048 (16.5)	7001 (28.5)	43 (37-50)	16425 (66.8)	6718 (27.3)	7.9
1	893	61 (6.8)	322 (36.1)	42 (35-49)	535 (59.9)	97 (10.9)	6.1
2	818	102 (12.5)	156 (19.1)	40 (35-47)	584 (71.4)	138 (16.9)	8.3
3	728	103 (14.1)	183 (25.1)	45 (37-52)	458 (62.9)	134 (18.4)	9.0
4	732	191 (26.1)	265 (36.2)	45 (38-50)	533 (72.8)	208 (28.4)	6.7
5	739	92 (12.4)	249 (33.7)	43 (37-50)	445 (60.2)	185 (25.0)	5.8
Etc …							

**
*Power.*

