** To estimate power, we simulated the study assuming that iHOST reduces the risk of each outcome by 5 percentage points (for example from 20% to 15%). For the “pre iHOST” data, we used the calendar year 2021 (summarised in
Table 2). For the "post iHOST” data, we used same dataset; but with outcomes randomly generated where the risk of each outcome was the hospital-specific risk from 2021, reduced by 5 percentage points for the iHOST sites. An example of a single simulation is shown in
Figure 3. We repeated this simulation 1,000 times and calculated the proportion of simulations in which a significant result was found (ie. p <0.05). This suggested good power to detect a risk reduction of 5 percentage points when results from the three hospitals are pooled, but low power at individual sites. Code for the power analysis is available at
https://github.com/[name]/ihost/tree/main/power.

**Table 2. T2:** Power of the iHOST study to detect an absolute reduction in outcomes of five percentage points.

	Patient-directed discharge	28-day emergency readmission
Site A	0.475	0.228
Site B	0.839	0.442
Site C	0.837	0.376
Pooled effect	>0.999	0.921

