We will evaluate the intervention using a pragmatic mixed-methods approach. This will provide a holistic understanding of the intervention’s costs and benefits. We chose this approach over a cluster randomised trial for three reasons. First, such a trial would be expensive. Second, the barriers to implementation are different in each hospital and iHOST is focused on developing an intervention that is suitable for each site, rather than a consistent intervention. Third, we do not necessarily expect a clear effect on a single primary outcome. Given the marginalisation of the patient group and the long histories of adversity that many have experienced, it is possible that many patient-directed discharges will occur despite better OST and better patient care. Our engagement with patients and staff suggests that better OST could reduce suffering and increase trust between staff and patients even if primary outcomes in our quantitative study do not appear to change significantly. We wanted to capture these holistic outcomes.

Key limitations are:

1. 

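### The plan analyses two unranked primary outcomes separately at three hospitals, but claims good power for a pooled effect that the analysis does not plan; no result is named as decisive

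*Protocol article*

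**What the plan says.** - **Outcomes.** Protocol article, Abstract, Methods: "The primary outcomes for the quantitative study are patient-directed discharge and emergency readmission within 28 days". The Study design paragraph of the difference-in-difference section names the same two, again without an order.
- **Hospitals.** Population paragraph: "We will include patients from the three iHOST sites and from the 50 largest acute hospitals in England" that are not implementing iHOST.
- **Unit of analysis.** Because the launch dates differ, the Analysis paragraph says "the analysis will therefore be done separately for each hospital".
- **Effect parameter.** The same section states: "The effect of iHOST will be interpreted from the interaction between time and the control/intervention indicator".
- **Significance criterion.** It appears once, in the Power paragraph, where the authors "calculated the proportion of simulations in which a significant result was found (ie. p <0.05").
- **Power.** Table 2 gives a value for each site and a pooled value for each outcome. The accompanying text claims good power for the pooled result and low power for single sites.
- **Interpretation.** The Discussion explains why a cluster randomised trial was not chosen and remarks that "we do not necessarily expect a clear effect on a single primary outcome". The Impact paragraph of the abstract says: "Depending on the results, we will promote the intervention at hospitals across the UK".

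**The concern.** The Analysis paragraph fixes six interaction estimates: two outcomes at each of three hospitals. The Power paragraph justifies the study on two other estimates, one pooled effect per outcome, and the model description provides for no pooled fit or combination of site results. The article does not say whether the six or the two carry the conclusion, or how the two primary outcomes relate to each other.

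Two things are at stake. If the intervention does nothing, several results are available and any one of them could be presented as the finding. If it works equally well everywhere, the site results will probably disagree, and without a named main result the conclusion would be settled after the data are seen. The cost-consequence analysis also needs numbers of discharges and readmissions prevented, and the article does not say whether site or pooled estimates supply them.

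**Working it through.** **Inputs.** Two primary outcomes (Abstract). Three hospitals analysed separately (Analysis). A level of 0.05 per test (Power), taken as two-sided because the article does not say. Table 1: 349, 662 and 624 patients at sites A, B and C; 24,604 controls. Table 2 powers for a 5-point reduction: patient-directed discharge 0.475, 0.839, 0.837, pooled >0.999; readmission 0.228, 0.442, 0.376, pooled 0.921. Assumed, because the article does not give it: a correlation between the two outcomes' test statistics of 0 to 0.8.

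**1. Table 2.** The closed form nearest to the described simulation treats the pre-period data as fixed and uses a common residual variance. Power = Φ((0.05 − 1.96·SE)/SD), with SE² = p_c(1−p_c)(2/n + 2/24,604) and SD² = q(1−q)/n + p_c(1−p_c)/24,604. Here p_c is the control risk and q is the site risk minus 0.05.

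| | A | B | C | Pooled |
|---|---|---|---|---|
| Discharge, Table 2 | 0.475 | 0.839 | 0.837 | >0.999 |
| Discharge, closed form | 0.390 | 0.738 | 0.726 | 0.995 |
| Readmission, Table 2 | 0.228 | 0.442 | 0.376 | 0.921 |
| Readmission, closed form | 0.225 | 0.517 | 0.483 | 0.952 |

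The table is not reproduced. That is not evidence of an error: the authors simulated from patient-level data with hospital-specific risks, and most control-hospital rows are not printed. The steps below take Table 2 at face value.

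**2. False positives under a global null, if any one significant result counted.**
- Six independent tests: 1 − 0.95⁶ = 0.265.
- Shared controls make the site tests correlate by (1/24,604)/√[(1/n₁+1/24,604)(1/n₂+1/24,604)], which is 0.019 to 0.025. Simulation (1,000,000 multivariate normal draws) with these values gives 26.4%, 24.8% and 21.6% at between-outcome correlations of 0, 0.5 and 0.8.
- Two pooled tests: 1 − 0.95² = 9.75% at correlation 0; simulated 9.1% at 0.5 and 7.8% at 0.8.
- Site and pooled tests all counted: 29.4%, 27.5% and 23.8%.
- Six site tests, false claim of benefit only: 1 − 0.975⁶ = 14.1% if independent, 11.1% at correlation 0.8. A single test gives 2.5%.

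**3. Disagreement between sites under a true uniform 5-point effect.** With sites treated as independent, P(mixed) = 1 − P(all significant) − P(none significant).
- Discharge: 1 − 0.475×0.839×0.837 − 0.525×0.161×0.163 = 1 − 0.334 − 0.014 = 0.653.
- Readmission: 1 − 0.228×0.442×0.376 − 0.772×0.558×0.624 = 1 − 0.038 − 0.269 = 0.693.

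**4. Power after adjusting the two pooled tests.**
- At level 0.025, pooled readmission power is Φ(1.412 + 1.960 − 2.241) = Φ(1.131) = 0.87. Discharge, taking 0.999 as its floor, is Φ(3.090 + 1.960 − 2.241) = Φ(2.809) = 0.997.
- Under Holm, readmission is tested at 0.05 whenever discharge passes at 0.025, so with these powers it stays at about 0.92. The 0.87 is the value if the discharge test gives no help.
- The conversion assumes that the estimate's SD equals its SE. With the SD at about 0.7 of the SE, as when pre-period data are held fixed, the lower value is Φ(1.412 − 0.281/0.7) = Φ(1.01) = 0.84.

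**The case against.** The strongest reply is that multiplicity rules usually belong in a statistical analysis plan, which is not shown, and that an article condenses. That stands for the adjustment method: its absence alone would be no finding. It does not dispose of the mismatch, because the article itself fixes the unit of analysis as the single hospital, with a reason, and then rests its power claim on a different unit.

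A reader might infer a stronger charge: that the plan tests six hypotheses at 0.05 and so carries a 25% error rate where 5% was promised. The article does not support this. The phrase "a significant result was found (ie. p <0.05") describes how simulations were counted; it is not a decision rule for the final analysis. No family-wise level is claimed. The linear probability model is motivated by estimating absolute risk differences. If the pooled effects decide, the relevant figure is 9–10%.

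A reader might also infer that UK-wide promotion hangs on one significant result. The Impact sentence concerns the whole mixed-methods project, and the Discussion allows for benefit even where the primary outcomes do not change significantly.

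Separate site estimates are also reasonable in themselves, since launch dates differ and the intervention is adapted to each hospital. That is a reason to report them. It does not say which result answers the main question. Low power at single sites is already disclosed; the calculation in step 3 adds only what that implies for agreement between sites.

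**Conclusion.** The point holds as an unreconciled conflict. The Analysis paragraph plans six site-by-outcome contrasts, the Power paragraph relies on two pooled effects, the two primary outcomes are unranked, and no result is named as the main one.

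The 22–26% and 9–10% figures are conditional. They assume no effect on either outcome at any site, a valid two-sided 5% level for each test, and a reading in which any one significant result counts as positive. The first range spans between-outcome correlations of 0 to 0.8. The second spans 0 to 0.5, and falls to 7.8% at 0.8. The 65% and 69% rest on Table 2 as printed, a uniform 5-point effect and independent sites.

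The figures show why the choice needs fixing in advance. They do not measure an error rate that the article has adopted.

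**What to change.** 1. In the Analysis paragraphs, define one all-sites effect per outcome as the main analysis, state how the three hospitals are combined given their different launch dates, and make it the same quantity as the pooled row of Table 2.
2. State how error is controlled over the two primary outcomes. Holm is enough and needs no ranking.
3. Keep the six site-by-outcome estimates, reported with 95% confidence intervals and labelled descriptive.

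**Cost.** Wording only; no new data or patients. Single-site p-values lose confirmatory standing. Readmission power may fall slightly: on Table 2 it stays near 0.92 under Holm, with about 0.87 if the discharge test gives no help (0.84 under the alternative variance assumption in the working). Patient-directed discharge stays above 0.99.

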**Impact:**

We anticipate that iHOST will improve care for hospital patients who use illicit opioids and/or are receiving community-based opioid substitution therapy. Depending on the results, we will promote the intervention at hospitals across the UK. Dissemination, including through publication, will inform hospital-based services for people who use drugs both in the UK and other countries.

## Introduction

People who use illicit opioids such as heroin have a high rate of hospital admission, particularly due to injecting-related and respiratory infections, exacerbations of chronic respiratory diseases, and gastrointestinal problems related to hepatitis and comorbid alcohol dependence
^
1–
3
^. In the UK the population using illicit opioids is ageing due a peak in initiation of heroin use in the 1980s and 1990s
^
4,
5
^. Management and acute treatment of long-term conditions is therefore becoming a more important issue in this population.

Many people who use illicit opioids report poor experiences when admitted to hospital. Qualitative research has found evidence of stigma among hospital staff, diagnostic overshadowing (in which symptoms are attributed to drug use and not investigated to the same extent as other patients), poor pain relief, and limited availability of opioid substitution therapy (OST)
^
6–
10
^. OST (also known as ‘opioid agonist therapy’ or ‘medication treatment of opioid use disorder’) is a medical intervention that includes prescription of opioids such as methadone or buprenorphine to alleviate opioid withdrawal, reduce illicit drug use, and help provide stability
^
11
^. In the UK, it is typically managed in community-based clinics, and at the time of writing (2024), methadone is the most prescribed medicine, and buprenorphine is less commonly used. While data on the relative use of methadone and buprenorphine in OST in the UK is not readily available, some hospital guidelines for management of substance dependence do not mention buprenorphine
^
12
^. Research in the UK and internationally shows that lack of OST in hospitals is a key barrier to hospital care and means that people are reluctant to go to hospital until symptoms are severe, or may leave hospital before completing treatment to access illicit opioids (a scenario called ‘patient-directed discharge)
^
8,
13,
14
^.

Outcomes for this patient group are poor. For example, approximately 10% of inpatient admissions among people with a history of using illicit opioids end in patient-directed discharge (compared to approximately 1% of all admissions)
^
15–
17
^; 80% of admissions are unplanned (compared to 50% for all hospital inpatients of the same age
^
18
^); and the risk of fatal opioid overdose is four times greater in the two weeks after hospital discharge than at other times
^
15
^.

Various initiatives have been established to improve OST and care for hospital patients who use illicit drugs
^
19
^. These include addiction liaison teams, in which multidisciplinary specialists support ward staff to care for patients who use drugs and alcohol; bridge clinics, which aim to link patients with community addiction services and provide addiction treatment while these linkages are being made; and training for general medical staff
^
19,
20
^. These initiatives have mostly been studied in North America. The ‘Improving Hospital Opioid Substitution Treatment’ (iHOST) project is working with three acute hospitals in England to develop, test, and evaluate an intervention to improve opioid withdrawal management and OST provision in acute NHS Hospitals.

## Protocol

### Patient and public involvement

The project stemmed from community-identified need, and intervention components were co-produced with people who use heroin and/or receive OST. Our advisory board members, peer researchers, and investigators also include people with past and current experience of opioid use to ensure community accountability. Some of authors listed on the present paper have past or current experience of opioid use.

In quarterly workshops throughout the project we will work with a group of ‘peer experts’ (people who currently use opioids or are on OST) to discuss project progress and findings and iteratively co-create a cultural safety framework to inform hospital care for people who use opioids in England. This participatory approach is core to the iHOST project.

Cultural safety principles focus on the way dominant cultural expectations of healthcare can be experienced as unsafe by marginalised groups
^
21–
24
^. Cultural safety principles aim to reduce health care practices that cause marginalised patients to feel unsafe and powerless. Developed by nurse academics working with Maori patients in New Zealand, this approach has been translated widely, including for practitioners working with people who use drugs in North America.

### Aims and objectives

iHOST aims to improve OST in hospital settings to: (1) reduce barriers to hospital presentation and reduce delayed presentations, (2) improve care, (3) reduce patient-directed discharges, and (4) reduce emergency readmissions. The research objectives are to: (1) optimise iHOST components and test feasibility in a London hospital and associated local drug services; (2) evaluate intervention acceptability, fidelity, reach, costs, and impact; (3) develop and disseminate toolkits for national implementation.

### The intervention

We will develop and evaluate an intervention (iHOST) to improve OST in acute hospital settings. iHOST will be implemented at three acute hospitals in England: University College London Hospital, St. James University Hospital Leeds, and Royal Stoke University Hospital. The project will be developed in partnership with local drug treatment services. The intervention primarily aims to improve continuation of OST from community to hospital settings but will also inform OST initiation and discharge planning for patients who were not already in receipt of community-based OST. The programme phases are shown in
Figure 1, and launch dates are currently anticipated to be:

University College London Hospital: November 2022 (already launched at the time of publication)St James University Hospital Leeds: January 2024Royal Stoke University Hospital: January 2024

